## Abstract

**Background:**

Receiving a diagnosis of lung cancer is an emotional event, not least because it is usually diagnosed at advanced stages with limited life expectancy. Although evidence-based educational, emotional, and social interventions exist, they reach few patients and usually when it is too late.

**Objective:**

This project will be carried out in a comprehensive center for cancer care and health research, aiming to study the efficacy, costs, and utility of an eHealth ecosystem to meet the psychosocial needs of patients with advanced lung cancer.

**Method:**

We will enroll 76 patients with advanced lung cancer into an eHealth ecosystem of stepped and personalized psychosocial care for 9 months. These patients will be compared with another 76 receiving usual care in a non-inferiority randomized controlled trial. The following main outcomes will be measured every 3 months: emotional distress, spirituality, demoralization, quality of life, and medication adherence. Secondary outcomes will include symptomatology, health education, cost-utility analyses, usability and satisfaction with the platform, and time to detect emotional needs and provide care. Baseline differences between groups will be measured with the Student *t-*test or chi-square test, as appropriate. We will then compare the main outcomes between groups over time using multilevel linear models, report effect sizes (Hedges' *g*), and assess non-inferiority. The cost-utility of both interventions will be considered in terms of quality adjusted life years and quality of life given the costs of providing each treatment.

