### Inclusion and exclusion criteria

2.3

Individuals agreeing to participate will be screened to verify whether they meet all the following inclusion criteria: age ≥ 18 years; recent diagnosis (<3 months) of advanced lung cancer (stage III–IV); internet access and digital experience; and ability to read, write, and speak Spanish. The exclusion criteria will include current major depressive episodes, risk of self-harm, active psychotic symptoms, and substance abuse.

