### Timeline

2.4

At the baseline visit, researchers will explain the study and obtain informed signed consent. They will then introduce the patient to REDCap, a secure web platform for building and managing online databases and surveys (https://www.project-redcap.org/). After checking eligibility at baseline, patients will be randomly allocated to one of the two treatment arms by REDCap, using simple randomization. The clinician-administered face-to-face questionnaires will be administered to all patients at this baseline evaluation (T0), while REDCap will send self-administered measures by e-mail at baseline (T0), 3 months (T1), 6 months (T2), and 9 months (T3) (Fig. 1).

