### Planned statistical analysis

2.9

Descriptive analyses will be performed using Student t or chi-squared tests, as appropriate. This will include assessment of sociodemographic and clinical variables at baseline, together with any pre-treatment differences between groups. Intention-to-treat analyses will then be performed through multilevel linear models to compare both groups on each primary outcome: emotional distress (HADS), demoralization (DS-II), QoL (FACT-L), and medication adherence (ARMS-e).

The modeling process will be parsimonious and guided by fit indexes, starting with a model using the time and type of therapy as fixed predictors. Then, random effects will be tested, and the interaction between time and type of therapy, the eHealth step reached, symptomatology (ESAS-r), and spirituality (FACIT-Sp) will be progressively entered as predictors. The estimation method will be maximum likelihood. Effect sizes (Hedges' g) will be reported for the primary outcomes and non-inferiority will be assessed for the HADS by comparing the means of both groups at T2 and T3. Additional multilevel linear models will be run to assess changes in health education (VAS) between groups, according to the same procedures. As for the cost-utility analyses, the EQ-5D will be used to compute the QALYs together with associated costs for medical care, psychotropics, sick leave, professional salaries, infrastructure, and transportation.

Descriptive analyses will also be conducted for platform's satisfaction and usability (VAS), as well as for participants reaching each step in the eHealth group. Mean differences in the number of clinical cases detected (according to the emotional thermometer), waiting time to provide care, and number of clinical cases solved will then be compared between groups by Student *t*-tests. For the reporting of results, 95 % confidence intervals will be provided. Analyses will be performed using IBM SPSS version 24 (IBM Corp., Armonk, NY, USA) and R software, with support provided by the biostatistics department of IDIBELL.

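### Baseline arms are compared by significance tests that lead nowhere, while the HADS non-inferiority comparison at T2 and T3 names no baseline covariate, neither stage (III vs IV) nor baseline HADS

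*Protocol article*

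**What the plan says.** The abstract (Method) states "Baseline differences between groups will be measured with the Student" t-test or chi-square test. Section 2.9 (Planned statistical analysis) repeats those tests and adds: "This will include assessment of sociodemographic and clinical variables at baseline, together with any pre-treatment differences between groups". Neither place says what follows from a significant or a non-significant result.

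Section 2.3 (Inclusion and exclusion criteria) admits patients with a "recent diagnosis (<3 months) of advanced lung cancer (stage III–IV"), so stage is known for every patient before allocation. Section 2.4 (Timeline) states that "patients will be randomly allocated to one of the two treatment arms by REDCap, using simple randomization".

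For the primary outcomes, section 2.9 describes multilevel models fitted by maximum likelihood, "starting with a model using the time and type of therapy as fixed predictors". Random effects are tested next, and then "the interaction between time and type of therapy, the eHealth step reached, symptomatology (ESAS-r), and spirituality (FACIT-Sp) will be progressively entered as predictors", guided by fit. On the key claim it says that "non-inferiority will be assessed for the HADS by comparing the means of both groups at T2 and T3". Stage appears in none of these statements, and the T2/T3 comparison names no covariate.

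**The concern.** After random allocation, any baseline difference is due to chance. A test of that hypothesis asks a question already answered, and a non-significant result does not show that an imbalance is harmless. The test is also a weak screen at 76 per arm.

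The listed predictors do not fill the gap:

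- The eHealth step reached arises after randomisation, and only in one arm.
- ESAS-r and FACIT-Sp are repeated outcome measures. Section 2.9 does not restrict them to their T0 values, and their entry depends on fit.

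No fixed baseline prognostic factor is therefore committed to. The most exposed result is the one the trial exists for, the HADS comparison of means at T2 and T3. If stage affects distress at 6 and 9 months, a chance excess of stage IV in one arm shifts that comparison. If stage also predicts who stops answering, a likelihood-based model without it makes the missing-at-random assumption harder to defend. The plan itself expects 25% dropout (section 2.7).

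**Working it through.** **Inputs from the protocol.** Section 2.7 gives a margin of 5 HADS points, one-sided α of 2.5%, power of 80%, dropout of 25%, and 76 per arm (152 in total). Section 2.4 gives simple randomisation.

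**Assumptions, not in the documents.** Stage IV share 50–80%; stage IV patients score 1–4 HADS points higher than stage III.

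**1. The plan's own figure.** No SD is stated, so 152 cannot be reproduced from stated inputs alone. Working backwards, 76 × 0.75 = 57 evaluable per arm. The implied SD is 5 × √(57/2) / (1.960 + 0.842) ≈ 9.53. Forwards, SD 9.5 gives 57 evaluable per arm, then 57/0.75 = 76, or 152 in total. This SD is used below.

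**2. Size of a chance stage imbalance.** With stage IV share p and n = 76 per arm, the SD of the difference in shares is √(2p(1−p)/n). The largest split that an uncorrected chi-square test leaves at p ≥ 0.05, and the resulting shift (imbalance × stage effect), are:

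| Stage IV share | SD of imbalance (points) | Largest non-significant split | Imbalance (points) | HADS shift, 1-point effect | HADS shift, 4-point effect |
|---|---|---|---|---|---|
| 50% | 8.1 | 44 v 32 | 15.8 | 0.16 | 0.63 |
| 60% | 7.9 | 51 v 40 | 14.5 | 0.14 | 0.58 |
| 70% | 7.4 | 58 v 48 | 13.2 | 0.13 | 0.53 |
| 80% | 6.5 | 65 v 57 | 10.5 | 0.11 | 0.42 |

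The largest shift is 0.63/5, about 13% of the margin. The average absolute imbalance (0.798 × SD) gives shifts of 0.05–0.26 points. For a 60–70% stage IV share, simulation puts the chance of an imbalance of at least 10 points at 18–21%.

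**3. The baseline test as a screen.** At 76 per arm, the power to flag 65% v 75% is 27%, 65% v 80% is 54%, and 65% v 85% is 82%.

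**4. Effect on the non-inferiority test, given an imbalance.** Take p = 0.7, 57 evaluable per arm, a 15-point imbalance and a stage effect g of 2–4 points. The shift is 0.15 × 2 = 0.3 to 0.15 × 4 = 0.6. The within-stage SD is √(9.53² − g²p(1−p)). By normal approximation:

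| Direction | One-sided error at the margin (nominal 2.5%) | Power at no difference (nominal 80%) |
|---|---|---|
| eHealth arm has fewer stage IV | 3.6–4.9% | 84–88% |
| eHealth arm has more stage IV | 1.6–1.0% | 75–70% |

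**5. Over all randomisations.** In 200,000 simulated trials for each stage effect tried (0, 2, 3 and 4 points), the unadjusted test keeps error at about 2.5% and power at about 80%.

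**6. Precision gained by adjusting for stage.** The variance removed is g²p(1−p)/SD². For g = 2 this is 4 × 0.21/90.8 = 0.9%; for g = 4 it is 16 × 0.21/90.8 = 3.7%.

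**The case against.** The strongest reply is that this is a condensed article. Covariate lists are commonly left to a full protocol or SAP, and nothing in section 2.9 forbids adding stage. The absence of stage alone would indeed be no finding. But the article does state its method: baseline tests, a list of predictors, and a comparison of means. The point is an improvement to that stated method.

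Three stronger readings are tempting, and the documents do not support them.

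- A reader might infer that a significant imbalance would be adjusted for and a non-significant one would slip through. Section 2.9 treats the tests as descriptive and ties no decision to them, so p = 0.05 is not a dividing line.
- A reader might infer that a stage imbalance enters every arm comparison in full. The outcomes are also measured at T0, and the models can include time by therapy. In change-over-time contrasts a baseline outcome difference is then separable, and only a stage effect on trajectory remains. ESAS-r may also carry part of a stage effect.
- A reader might infer that the trial's error rate is inflated. Step 5 shows that it is not; the standard error already reflects chance imbalance.

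It is also fair to say that the stage shares and effects are assumed, and that a small stage effect makes the matter trivial. That stands, and it sets the weight of the point.

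**Conclusion.** The point holds as a free improvement; it does not show that the design is invalid. The baseline tests cannot show comparability and lead to no stated action. The T2/T3 HADS comparison is the most exposed result because it names neither stage nor baseline HADS.

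The cost of leaving it so is modest. Under the assumed 1–4-point stage effect, an imbalance of 10–16 points shifts the HADS difference by about 0.1–0.6 points against a margin of 5. Given an imbalance near the top of that range and an effect of 2–4 points, conditional one-sided error reaches 3.6–4.9% or conditional power falls to 75–70%, depending on direction. Adjusting for stage removes only about 1–4% of the variance. That stage predicts dropout is likely, but it too is an assumption.

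**What to change.** - Describe the arms at baseline with means, percentages and standardised differences, and drop the between-arm significance tests.
- Prespecify stage (III vs IV) and the T0 HADS score as fixed covariates in the T2/T3 non-inferiority estimate. If that estimate comes from the longitudinal model, T0 may stay as a response instead of a covariate.
- Include stage in the other arm-comparison models too.
- Apply the adjustment whatever imbalance is observed.

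Leave the randomisation scheme as it is. Stratified permuted blocks, brought in during recruitment to an open-label trial in one centre, could make allocations more predictable, and covariate adjustment does not need them.

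The cost is a sentence or two in the analysis section and one or two degrees of freedom per model (slightly more if stage is also allowed to act on change over time). No new data are needed, since stage is an eligibility item and the T0 outcomes are already collected.

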**Discussion:**

This randomized controlled trial should provide new evidence on the efficacy and cost-utility of an eHealth ecosystem to deliver personalized and timely psychosocial care to patients with advanced lung cancer.

**Trial registration:**

ClinicalTrials.gov ID “NCT05497973”.

## Introduction

1

Lung cancer affects >2 million people worldwide each year and has a 5-year patient survival of only 13 % (Sung et al., 2021). Estimates in the European Union indicated that there had been 318,327 new cases in 2020, marking the lung as having the highest mortality of 20.4 % of all cancer-related deaths (European Union, 2021). Affected patients also frequently encounter severe symptoms that show a variable and erratic course over time and make the illness course highly unpredictable. Consequently, these patients tend to have a very poor quality of life (QoL), especially in advanced stages (Presley et al., 2020), and up to 63 % experience clinically significant psychological distress (Graves et al., 2007; Lv et al., 2021). Indeed, a recent survey of over 9000 patients with lung cancer indicated that most functional limitations were due to pain (68.6 %) or emotional distress (48.3 %) that remained untreated in 32.5 % (Presley et al., 2020). Psychosocial care is generally inadequate, with many patients having no possibility of receiving appropriate care. Given that this distress does not remit over time (Aubin et al., 2022), it is urgent that we improve screening, offer close and intensive follow-up, and refer to adequate and accessible services early.

Palliative care refers to the medical relief typically offered to people living with incurable illnesses, and for those with advanced lung cancer, it typically focuses on common physical symptoms like fatigue, dyspnea, and chronic pain (Rajapakse, 2021). Over recent decades, however, the value of addressing a person's psychosocial and spiritual needs has also been recognized. American and European societies for medical oncology now advocate the integration of early psychosocial palliative care in standard oncology practice for patients with metastatic or advanced disease. This decision has been supported by the results of a recent meta-analysis (Fulton et al., 2019), which demonstrated that palliative interventions with physical and psychological aspects can benefit a patient's short-term QoL and overall symptom burden. Evidence suggests that a patient's emotional distress is associated with not only poorer QoL but also lower adherence to treatment and the adoption of unhealthy lifestyles (Jansen et al., 2017). Despite this growing evidence, emotional distress is not always considered in palliative care, leaving many patients with undetected and unresolved psychosocial needs.

Distress is a common and frequently ignored psychosocial dimension in patients with advanced cancer, but evidence suggests it can be improved by including a consideration of QoL rather than survival in isolation (Reale et al., 2020). QoL is a broad concept that includes emotional well-being, self-care, and performing usual daily activities. It has been evidenced that patients with an enhanced sense of psycho-spiritual well-being can cope more effectively with a terminal illness and find meaning in the experience (Lin and Bauer-Wu, 2003). Indeed, several studies have found a relationship between greater spirituality and both QoL (Steinhauser et al., 2017) and emotional well-being (Moyano et al., 2019) during palliative care. By contrast, demoralization appears to be an important risk factor for patients' distress that negatively affects spiritual well-being (Liu and Hsiao, 2019). This is important because it reaches clinically significant levels in 13 %–18 % of patients with advanced cancer (Robinson et al., 2015). Other sources of distress include disinformation, poor health literacy, and issues with family communication. Nevertheless, each of these has shown improvement when addressed with psychosocial interventions (Graves et al., 2007).

Cancer-related distress affects both the emotional and physical statuses of patients, and together with inadequate social support, represent a major contributor to treatment adherence in patients with lung cancer (Liu et al., 2022). Similarly, depression is independently associated with not only treatment adherence but also with a poorer prognosis (Arrieta et al., 2013). Any holistic psychosocial intervention for patients with lung cancer should also consider health literacy, which itself is associated with medication adherence (Gönderen Çakmak and Uncu, 2020).

Despite the growing and evident health benefits of comprehensive palliative care interventions, various barriers exist to the implementation of psychosocial care in hospital settings. The most frequent of these are the failure to detect needs early, the long waiting lists, and the restricted mobility of many patients (Travado et al., 2017). To improve the implementation of psychosocial care, efforts have focused on improving its accessibility and efficiency by introducing early and tailored psychosocial interventions that are both customized to the patient and cost-efficient for service providers (Bekelman et al., 2016). It is here that information and communication technologies (ICTs) are now playing a pivotal role in health care (eHealth), offering a feasible solution that can ensure continuity of their care in patients with advanced cancer (Kroll et al., 2021). The use of eHealth can improve the monitoring of warning signs; facilitate better communication with professionals; and leverage clinical treatments that are cheaper and more accessible than traditional modalities (Penedo et al., 2020). Although this appears to apply to palliative care (Widberg et al., 2020), the few studies comparing eHealth with usual psychosocial interventions have found mixed efficacy in palliative settings (Escriva Boulley et al., 2018).

This clinical trial is preceded by a European-funded project (ONCOMMUN; https://oncommun.eu/) that developed an eHealth ecosystem for patients with breast cancer. This project aimed to facilitate early psychosocial care for patients with breast cancer via an online, stepped program implemented at the Institut Català d'Oncologia (ICO) through the ICOnnecta't program (Ochoa-Arnedo et al., 2020). The tiered intervention has four levels, starting with screening and monitoring of psychosocial needs and offering more intensive interventions as patients need them, and the last level is group psychotherapy. This has shown promising early results in breast cancer (Ciria-Suarez et al., 2022; Medina et al., 2022) and the potential to address the psychosocial needs in lung cancer (Graves et al., 2007). It is anticipated that a stepped, tailored, psychosocial eHealth intervention based on this model will detect distress in patients with lung cancer quickly and facilitate the provision of personalized solutions through psychological counseling, health literacy, and social support in the community. In turn, these can impact variables like demoralization, spirituality, and medication adherence.

### Aims and hypotheses

1.1

The main objective of the project is to implement and evaluate the efficacy of a stepped online ecosystem for detecting, following, and addressing the psychosocial needs of patients with lung cancer and to compare those with usual face-to-face treatment. We aim to detect cases at risk of significant emotional distress and decrease the time to access appropriate psychosocial care when using eHealth and usual face-to-face care.

Comparisons between the two interventions will consider the effects on ameliorating the psychosocial consequences of lung cancer and its treatment on emotional distress, demoralization, QoL, and medication adherence, including consideration of the role of spirituality and patient perception of their health education. The cost-utility of each intervention will then be analyzed in terms of quality adjusted life years (QALYs), considering use of additional health services, consumption of psychotropic drugs, sick leave durations, professional salaries, and infrastructure and transportation costs. We will then measure perceived satisfaction and usability of the eHealth ecosystem. Finally, the cases at risk of emotional distress will be detected earlier than treatment as usual. Consequently, using new technologies, we will decrease the time to access appropriate psychosocial care.

Considering previous results, the literature reviewed, and the objectives set forth, we hypothesized that two psychosocial treatments will improve emotional distress, demoralization, QoL, and medication adherence. Moreover, these improvements will be greater in patients with worse psychosocial results at baseline. For patients with a better baseline status, we expect the psychosocial interventions to exert a buffering effect despite disease progression. The eHealth ecosystem will obtain results equivalent to usual care for emotional distress, demoralization, QoL, and medication adherence. Spirituality at baseline, or its augmentation by psychosocial interventions, will predict better outcomes for emotional distress, demoralization, QoL, and medication adherence. Health education will improve markedly in the group allocated to the eHealth intervention. Compared with usual care, eHealth will have a superior cost-utility in terms of QALYs. Finally, users will be satisfied with the eHealth ecosystem and will perceive it as easy to use. The eHealth ecosystem will significantly improve the time to detection, intervention, and resolution of clinically significant psychosocial need compared to usual care.

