### Study design

2.1

This study proposes a randomized non-inferiority trial of an eHealth ecosystem compared to usual psychosocial care. The main outcomes will be assessed at baseline (T0), 3 months from T0 (T1), 6 months from T0 (T2), and 9 months from T0 (T3). Therefore, the design comprises two treatment conditions and four assessments. We chose the non-inferiority based on a literature review that indicated mixed and inconsistent results when comparing eHealth and face-to-face psychosocial interventions in cancer (Merluzzi et al., 2019; Singleton et al., 2022; Wang et al., 2020; Xu et al., 2019). Therefore, we do not hypothesize that our eHealth ecosystem will be more efficacious than usual care, but instead, aim to show that it is at least not inferior in terms of efficacy and efficiency. The methodology will adhere to the principles of Responsible Research and Innovation (RRI, European Commission, Directorate-General for Communication, 2013).

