### Power analysis

2.7

The sample size has been estimated using R software, setting a non-inferiority margin of 5 points on the HADS (Vaganian et al., 2020) with a power of 80 % and a one-tailed α of 2.5 %. Assuming a dropout rate of 25 %, we require 152 participants (76 per branch) to ensure a 95 % bilateral confidence interval that excludes the non-inferiority threshold.

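### Equivalence is hypothesised on four outcomes, but only the HADS has a margin and a non-inferiority test, and the lists of primary outcomes disagree

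*Protocol article*

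**What the plan says.** **Hypothesis.** Section 1.1 (Aims and hypotheses) states: "The eHealth ecosystem will obtain results equivalent to usual care for emotional distress, demoralization, QoL, and medication adherence".

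**Design.** Section 2.1 describes a non-inferiority trial. The authors do not expect superiority but "aim to show that it is at least not inferior in terms of efficacy and efficiency".

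**Margin and size.** Section 2.7 sizes the trial by "setting a non-inferiority margin of 5 points on the HADS", "with a power of 80 % and a one-tailed α of 2.5" per cent. No other outcome is given a margin. It continues: "Assuming a dropout rate of 25 %, we require 152 participants (76 per branch").

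**Analysis.** Section 2.9 uses multilevel linear models "to compare both groups on each primary outcome: emotional distress (HADS), demoralization (DS-II), QoL (FACT-L), and medication adherence (ARMS-e"). It promises Hedges' g for the primary outcomes and 95% confidence intervals, and it confines the non-inferiority assessment to HADS means at T2 and T3 (6 and 9 months).

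**Primary outcomes.** The abstract lists five: "The following main outcomes will be measured every 3 months: emotional distress, spirituality, demoralization, quality of life, and medication adherence". Section 2.5.1 places the same five instruments under its heading for primary outcomes. Section 2.9 names four. The fifth is treated differently there: "spirituality (FACIT-Sp) will be progressively entered as predictors".

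**The concern.** Equivalence is a two-sided claim and needs a margin on each side. Non-inferiority is one-sided and needs one margin. Section 1.1 makes the two-sided claim on four outcomes, while the rest of the article plans the one-sided test on one of them.

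For the other three outcomes the only inferential tool described is a model for a difference between arms. Such a model can show that the arms differ. It cannot show that they are close enough, because nothing defines close enough. The article gives no other criterion by which the hypothesis on these outcomes could be judged.

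At stake is what the trial may conclude about demoralization, quality of life and adherence, where a claim of equal effect would rest on no threshold set in advance. The disagreement over which outcomes are primary adds to this, because a reader cannot tell which comparisons are meant to carry the conclusion.

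**Working it through.** **1. Each outcome, side by side**

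| Outcome | Equivalence hypothesised (1.1) | Primary or main (abstract, 2.5.1) | Between-group model (2.9) | Margin (2.7) | Non-inferiority test (2.9) |
|---|---|---|---|---|---|
| HADS | yes | yes | yes | 5 points | yes, T2 and T3 |
| DS-II | yes | yes | yes | none | no |
| FACT-L | yes | yes | yes | none | no |
| ARMS-e | yes | yes | yes | none | no |
| FACIT-Sp | no | yes | not named; used as predictor | none | no |

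Three of the four equivalence hypotheses have neither a margin nor a matching test. One outcome listed as primary has no between-group comparison named in 2.9, although the abstract says that the main outcomes will be compared between groups.

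**2. The plan's own sample size**

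Inputs from 2.7: margin 5, one-sided α 0.025, power 0.80, dropout 25%. The article gives no SD, so 152 cannot be reproduced from stated inputs alone. With an assumed true difference of zero,

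n per arm = 2 × [SD × (1.960 + 0.842) / 5]², then divided by 0.75.

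| Assumed SD | n per arm | After dropout | Total |
|---|---|---|---|
| 7 | 31 | 42 | 84 |
| 8 | 41 | 55 | 110 |
| 9 | 51 | 68 | 136 |
| 9.5 | 57 | 76 | 152 |
| 10 | 63 | 84 | 168 |

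An SD of about 9.5 returns 152. That value is solved backwards and is an assumption. It shows only that 152 is a HADS non-inferiority sample size. The illustration in step 3 does not use it.

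**3. What a non-significant difference would tell us**

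Completers per arm: 76 × 0.75 = 57. In SD units, for an unadjusted comparison at one visit:

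- Standard error = √(2/57) = 0.187
- 95% interval half-width = 1.96 × 0.187 = 0.37
- P(non-significant) for a true deficit d = Φ(1.96 − d/0.187) − Φ(−1.96 − d/0.187)

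The deficits are assumed, to show a range. The last column repeats the sum for all 76 per arm, that is, with no dropout.

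| True deficit (SD) | 57 per arm | 76 per arm |
|---|---|---|
| 0.2 | 81% | 77% |
| 0.3 | 64% | 54% |
| 0.4 | 43% | 31% |

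**4. Equivalence on the HADS itself**

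If the trial has 80% power for non-inferiority at a true difference of zero, then two one-sided tests at 2.5% each, with the same margin on both sides, have power 2 × 0.80 − 1 = 0.60. The trial is therefore not sized for equivalence at that level, even on the outcome that has a margin.

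**The case against.** The strongest reply is that the confirmatory plan is coherent without the hypothesis sentence. The trial is sized on the HADS alone, non-inferiority is tested on the HADS alone, and both the design section and the conclusions speak of non-inferiority. On that view *equivalent* is one loose word in a list of expectations, and FACIT-Sp under the primary heading is a labelling slip, since 1.1 and 2.9 both treat spirituality as a predictor. Much of this stands. The HADS is in practice the confirmatory outcome, although no sentence says so. It lowers the severity but does not remove the contradiction.

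Three stronger readings are tempting, and the article does not support them.

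- A reader might infer that a non-significant difference will be taken as equivalence. No sentence says this, and the article promises effect sizes and 95% intervals. What can be said is that it offers no other criterion.
- A reader might infer that the three outcomes go untested. They do have between-group models. What they lack is a non-inferiority or equivalence test.
- A reader might infer an inflated false-positive rate from five co-equal primary outcomes. No rule lets success on any one of them count, FACIT-Sp has no planned test in 2.9, and a falsely significant difference is the opposite error to false equivalence.

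It is also fair to say that the precision figures are for a simple comparison. The planned multilevel model uses repeated measures and partial data from patients who drop out, so it may be somewhat more precise.

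Finally, margins for outcomes that do not drive the sample size are often left to an analysis plan. But 2.9 is not silent. It states where non-inferiority will be assessed, and that scope is narrower than the hypothesis. No further document can make both lists of primary outcomes true.

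**Conclusion.** The point holds as an inconsistency inside the stated plan and should be fixed. It does not undermine the planned HADS test or the sample size.

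The equivalence hypothesis cannot be established on DS-II, FACT-L or ARMS-e with the analyses described, and on the HADS the planned test supports non-inferiority only. With 57 completers per arm, intervals of about ±0.37 SD leave room for sizeable deficits behind a non-significant result. Those figures rest on the stated sample size and dropout, an unadjusted single-visit comparison, a normal approximation and deficits chosen for illustration. The 60% power in step 4 rests instead on the stated 80% and a true difference of zero.

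The conflict between five and four primary outcomes is a matter of fact and rests on no assumption.

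**What to change.** - In 1.1, replace the equivalence wording with non-inferiority on the HADS.
- Name HADS total, the outcome that the trial is sized on, as the sole confirmatory primary outcome.
- Report DS-II, FACT-L and ARMS-e as arm differences with 95% confidence intervals.
- State that no equivalence or non-inferiority will be concluded on any outcome without a prespecified margin.
- Make the abstract, 2.5.1 and 2.9 agree on whether FACIT-Sp is an outcome, a predictor or both. If it is an outcome, name its between-group comparison.

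The cost is wording in four places and fewer headline claims. The sample size and the HADS analysis do not change. The edits should be made before results are known.

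If the investigators want confirmatory claims on all four outcomes, the alternative is a justified margin and test for each, with a multiplicity rule. That costs more. At 80% power for each outcome, the chance of showing non-inferiority on all four is 0.80⁴ = 41% if they are independent, and higher if they are correlated.
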